a PCP. Potential participants will be told the research is being done to assess adherence to hypertensive medications and to evaluate how a writing exercise about values might affect blood pressure. If they express interest in the study, they will be asked to arrive approximately one hour prior to the visit in order to review study procedures and provide informed consent. (see Patient Informed Consent) Those who decide to participate will have their blood pressure measured by the research coordinator using guideline-recommended procedures. Next, participants will be given a pre-randomized, consecutively numbered packet – to ensure the research coordinator is blind to the condition - containing the study materials. Packets will contain either an intervention or control version of the values affirmation exercise. To ensure balanced randomization by race at each site, there will be a pre-randomized series of packets for participants who self-identify as white and another pre-randomized series for those who self-identify as African American. Additional surveys will include a baseline demographics questionnaire, a measure of past experiences of discrimination, and a self-reported adherence (Voils) measure. (Table 1) Where patients feel comfortable using a tablet device, surveys will be administered and data will be collected on the tablet via an online survey format and stored in REDCap. If they do not feel comfortable with this format, all surveys will be administered on paper only. The values affirmation exercise will always be administered on paper, and the research assistant will provide instruction and remain available, but the patient will complete the exercise on their own, at their own pace. In our pilot work, patients completed all study materials in ~30 minutes. Next, patients will undergo routine check-in procedures, which includes blood pressure measurement at all sites, and complete the scheduled visit with their provider.

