#### **F. Data Analysis Plan:**

**Sample size estimation.** For our primary analysis, we assume a three-level model, with patients nested within providers and providers nested within clinics. Assuming comparable variation in adherence and  $\alpha=0.05$ , a sample size of 960 subjects (240 each cell in values affirmation, or control; 480 African American, 480 white) will be required to detect an effect size of 0.26 difference in adherence between any two cells with a power of 80%. Based on the pilot study results, a 0.26 effect size is approximately a 4.7% absolute difference in adherence scores. Since randomization is at the patient level, the intraclass correlation coefficient for patients nested within clinicians will

have a negligible effect on power. We conservatively estimate an attrition rate (neither having a med refill within the system nor returning for follow up) over all sites of 15%. We therefore will enroll an additional 170 patients to compensate for this attrition, for a final sample size of 1,130. We will cap enrollment at 450 subjects per site to ensure generalizability of results.

For moderation hypotheses, the primary contrast of interest is the adherence difference between African Americans with high and low past experiences of discrimination (dichotomized scores for ease of interpretation) who receive the intervention. Using a median split on the discrimination scores, the sample size for this comparison would be 120 in each subgroup. This sample size will provide >80% power to detect a 0.37 SD difference in adherence. For the patient activation mediation analyses, a sample size of 480 (e.g. African Americans only) will provide >80% power to detect a 0.13 partial correlation between change in the patient activation and change in adherence, adjusting for other variables in the model; a sample size of 960 will provide >80% power to detect a .10 partial correlation. Parchman et al report a standardized regression coefficient of 0.16 between patient activation and the Morisky medication adherence scale. While our proposed analytic approaches differ, this gives some indication of the anticipated strength of the relationship.

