The primary outcome variable (adherence measured by pharmacy refills) is continuous; in the event that normality assumptions are not met we will use transformations to normalize distributions. For the primary comparisons, we will employ intent-to-treat analyses, although we expect few or none of the randomized patients to not complete an exercise. We will examine overall values affirmation effectiveness between the racial groups. We will next create models with adherence as the dependent variable including the potential moderator variable (prior experience of discrimination) then including the potential mediator variables (patient activation, attitude, social norms, perceived behavioral control, and anticipated emotion). Finally, we will explore whether the collected provider variables (racial bias, past cultural competency training, self-efficacy and racial mix of clinical site) moderate the relationships. We will also include patient gender and provider race as a possible moderating variables. We will use general (or generalized, for dichotomous outcomes) linear mixed models, examining alternative structures for the variance-covariance matrix for the level 1 model by comparing goodness of fit for the different models as well as model fitting diagnostics to assess for influential points, outliers, overdispersion and heteroscedasticity. We will employ methods that utilize all available data, assuming ignorable missingness.

In secondary analysis using the self-reported adherence measures, we will dichotomize the groups into non-adherent (score  $\geq 2$  on any "extent" item) and adherent. We will also compare the pill count measure of adherence to the pharmacy fill estimates of adherence for validation. For blood pressure, the secondary outcome, we will compare the index and follow-up visits using mixed effects repeated measures models with a patient random effect. All hypothesis tests will be two-sided with  $\alpha=.05$ . Statistical analysis will use SAS 9.4.

**Statistical Model for Primary Outcomes.** The structure of the data is hierarchical (patients nested within providers) and longitudinal (repeated measures on patients over time). Baseline (time 0) is defined as the adherence rate for the 12-months prior to the index visit.

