**Level 1 model.** Repeated measures within each patient will be modeled as a growth curve model (shown here) or repeated measures. Time will be coded 0 for baseline and days since baseline for all post-baseline measures. The outcome for patient  $i$  measured at time  $t$  in practice  $j$  is  $Y_{tij}$

$$Y_{tij} = \pi_{0ij} + \pi_{1ij}(\text{time})_{ij} + \varepsilon_{tij}$$

where  $\pi_{0ij}$  is the individual status at time 0,  $\pi_{1ij}$  is the linear growth rate for patient  $ij$ , and  $\varepsilon_{tij}$  is the term that represents the random deviation of observation  $t$  within patient  $ij$  from the predicted value.

**Level 2 model.** The patient level models specify the relationship between the patient-level coefficients and the coefficients in the Level 1 model. Intervention status will be coded 1, if intervention, 0, if control. Race (AA) will be coded 1, if African American; 0, if white. Interaction terms will be included to estimate differential intervention effects for AA vs white. Fixed patient-level covariates (not shown) will be included at this level.

$$\pi_{0i} = \beta_{00} + \beta_{01}$$

(Interv) +  $\beta_{02}$  (AA) +  $\beta_{03}$  (Interv x AA) +  $r_{0i}$

$$\pi_{1i} = \beta_{10} + \beta_{11}(\text{Interv}) + \beta_{12}(\text{AA}) + \beta_{13}(\text{Interv} \times \text{AA}) + r_{1i}$$

where  $\beta_{00j}$  represents the initial status of white, control patients within clinician  $j$ ,  $\beta_{01}$ ,  $\beta_{02}$ , and  $\beta_{03}$  represent baseline differences by intervention status and race.  $\beta_{10j}$  represents the linear growth rate for white control patients within clinician  $j$ ,  $\beta_{11}$  represents the difference in slope for white intervention vs controls,  $\beta_{12}$  represents the difference in slope for AA vs white control patients, and  $\beta_{13}$  represents the differential intervention effect for AA vs white patients within clinician  $j$ . The  $r$ 's are patient-level random effects.

**Level 3 model.** The provider level models specify the relationship between the provider-level predictors and the coefficients in the Level 2 model.

$$\beta_{00j} = \gamma_{000} + u_{00j}, \quad \beta_{01} = \gamma_{010}, \quad \beta_{02} = \gamma_{020}, \quad \beta_{03} = \gamma_{030}$$

$$\beta_{10j} = \gamma_{100}, \quad \beta_{11j} = \gamma_{110}, \quad \beta_{12j} = \gamma_{120}, \quad \beta_{13j} = \gamma_{130},$$

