where  $\gamma_{000}$  is the intercept in the provider level model for  $\beta_{00j}$  (i.e. initial status for white controls);  $\gamma_{010}$ ,  $\gamma_{020}$ , and  $\gamma_{030}$  represent overall baseline differences by intervention status and race.  $\gamma_{100}$  is the linear growth rate for white controls;  $\gamma_{110}$ ,  $\gamma_{120}$ , and  $\gamma_{130}$  represent differences in slope by intervention status, race, and both.  $u_{00j}$  is a provider random effect. Thus, hypotheses can be tested directly by examining coefficients for the terms above or by means of linear contrasts.

Mediator analyses for the adherence outcome will use methods that completely partition between and within patient effects, with *change in adherence* as the primary outcome and *change in PAM scores* (or other measure) as the primary independent variable.

In addition to the planned analyses above, several additional analyses will be conducted using the study's currently collected data. No new data or variables will be collected. The results of the analyses will be included in abstracts for meetings/conferences, and/or in manuscripts submitted for publication. The list of additional analyses are below:

1. **Social vulnerabilities to disparities and participant attrition:** To explore whether social vulnerabilities are associated with participant attrition in a randomized trial, we will examine the relationship between age, minority race-ethnicity, sex, financial strain, insurance status, unemployment and educational attainment with enrollee attrition over 6 months.
2. **Racial differences in theory-based constructs related to hypertension management:** To understand the extent to which attitudinal constructs predict adherence behavior across racial groups, we will estimate a model in which prior adherence is the primary variable that predicts current attitudes towards adherence, norms supporting adherence, and perceived

- behavioral control over adherence. Perceived discrimination will be explored as an additional predictive measure. Future analyses may be similar to those listed above but will instead examine the value of attitudes, norms, and perceived behavioral control in predicting medication adherence for each of the racial groups at 3- and 6-month follow-up.

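### The displayed primary model lets the randomised arms differ at baseline and tests a slope difference; with one follow-up value this is a change-score contrast, which is valid but less precise than adjusting for baseline and carries chance baseline imbalance

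*Protocol*

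**What the plan says.** All references are to the protocol, section F unless stated.

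- *Statistical Model for Primary Outcomes*: "Baseline (time 0) is defined as the adherence rate for the 12-months prior to the index visit". Baseline adherence is therefore an outcome value, not a covariate.
- *Level 1 model*: "Repeated measures within each patient will be modeled as a growth curve model (shown here) or repeated measures". Time is 0 at baseline and counted in days afterwards.
- *Level 2 model*: arm, race and arm × race enter both the intercept and the slope. Fixed patient covariates are to be added but are not named.
- *Level 3 model*: the intercept terms "represent overall baseline differences by intervention status and race". The only cluster term is a random intercept for provider. Hypotheses are to be tested on these coefficients or on contrasts of them.
- *Sample size estimation*: the planned total of 960 "will be required to detect an effect size of 0.26 difference in adherence between any two cells with a power of 80" per cent. The split of that total is given as "240 each cell in values affirmation, or control; 480 African American, 480 white". The structure assumed there is "patients nested within providers and providers nested within clinics".
- *Statistical Analysis*: "All hypothesis tests will be two-sided with" α = 0.05.
- Section B, *Patient recruitment and procedures*: "To ensure balanced randomization by race at each site, there will be a pre-randomized series of packets" for each racial group.

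The number of follow-up values is described in two ways. Section A (*Primary Outcome*) sets the prior 12 months against the six months after the visit, which gives one follow-up value. The RE-AIM part of section C has adherence at baseline, 3 and 6 months and plans to examine whether the effect lasts or fades.

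**The concern.** Patients are randomised within race, so the arms have the same expected baseline adherence. A model that estimates a baseline arm difference anyway does not use that knowledge. It measures the effect as movement from each arm's own observed starting point, so an arm that starts low by chance is credited with the gap. At stake are precision for H1 and H3, and an estimate that depends on the luck of the draw at baseline.

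The open choice between growth curve and repeated measures does not remove this, because nothing in the text makes the baseline arm means equal under either form.

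Three lesser points follow from the same equations:

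- A straight line in time may not suit an exercise given once.
- The random effects may be too many for the data.
- The cluster levels differ from those in the sample-size paragraph.

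**Working it through.** **1. The plan's own figures.** Inputs from *Sample size estimation* and *Statistical Analysis*: effect 0.26 SD, two-sided α 0.05, power 80%, 240 per cell, attrition 15%.

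- n per cell = 2(1.96 + 0.84)² / 0.26² ≈ 233, against 240 stated.
- Power at 240 = Φ(0.26/√(2/240) − 1.96) = 81.3%.
- Enrolment = 960/0.85 ≈ 1,130.
- Implied SD = 4.7/0.26 = 18.1 points. The root mean square of the four pilot SDs (22, 14, 18, 17) is 18.0.

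The design was thus sized on the SD of a single adherence value with no baseline adjustment. The same n fits a change score only if ρ = 0.5.

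**2. What the displayed model estimates.** With one follow-up value, complete pairs and arm-specific intercepts, the slope difference times the follow-up time equals (follow-up − baseline) in one arm minus the same in the other. That is the difference in mean change.

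**3. Precision.** In units of SD², assuming equal variances before and after, the per-patient variance is 2(1 − ρ) for change and 1 − ρ² for baseline-adjusted. The ratio is 2/(1 + ρ), above 1 for every ρ below 1. Power = Φ(0.26/√(2v/240) − 1.96), where v is that variance:

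| ρ (assumed) | Variance ratio | Power, change | Power, adjusted |
|---|---|---|---|
| 0.3 | 1.54 | 67.3% | 84.7% |
| 0.4 | 1.43 | 73.9% | 87.4% |
| 0.5 | 1.33 | 81.3% | 90.8% |
| 0.6 | 1.25 | 89.0% | 94.5% |
| 0.7 | 1.18 | 95.7% | 97.9% |

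For an H3 interaction of 0.26 SD, change v adjusted is 39.8% v 56.0% at ρ = 0.3, 52.2% v 64.3% at 0.5 and 73.9% v 80.5% at 0.7.

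**4. Chance imbalance.** One standard error of the baseline arm difference is 18.08 × √(2/240) = 1.65 points. Given an imbalance of that size, the change estimate is off by (1 − ρ) × 1.65, which is 1.16, 0.83 and 0.50 points at ρ = 0.3, 0.5 and 0.7. The target effect is 4.7 points.

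**5. The pilot as illustration** (section II, pilot work). Intervention went from 74% to 83%, control from 83% to 81%.

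- Change contrast: (83 − 74) − (81 − 83) = 11 points.
- Raw follow-up difference: 83 − 81 = 2 points.
- Approximate adjusted estimate: 2 + 9b, where b = ρ × 15.57/20.10 (pooled after and before SDs). This is 3.4 points at ρ = 0.2 and 7.6 at ρ = 0.8.

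**6. If 3- and 6-month values are both used.** The least-squares slope over days 0, 90 and 180 has weights proportional to −90, 0 and +90, so month 3 has no weight (about none if visit days vary). In units of the 3-month effect, slope × 180 is 1.0 for a sustained step, 0.5 for half decay and 0 for full decay. An effect of 0.26 SD at month 3 and 0 at month 6 gives a slope effect of 0, while the mean over the two times is 0.13.

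**7. If one 6-month value is used.** Two values per patient give three second moments: two variances and a covariance. The random intercept, random slope, their covariance and the residual are four parameters, so they cannot all be estimated.

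**8. Site.** Trials were simulated at ρ = 0.5, 3,000 per setting. With assumed site shifts of 0.4 SD, change-score power is 81.5% with or without a site term. With further site-by-time shifts of 0.2 SD it is 80.2% without and 81.1% with. For the adjusted contrast the same two settings give 90.1% v 90.9% and 88.5% v 90.7%.

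**The case against.** The protocol declares change in adherence as the primary outcome (section IV, *Overall strategy*, and section A), and a difference in change answers exactly that. It is unbiased over randomisation. Preferring adjustment is an argument about efficiency and about the estimate conditional on the observed baseline. This stands: a reader might infer that the primary test is biased or invalid, and the document does not support that.

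The shortfall below 80% rests on an unknown ρ. This stands too: at ρ = 0.5 or more the change form reaches the stated power.

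The pilot can mislead. A reader might take 2 points as the true effect and 11 as an artefact. The raw follow-up difference is distorted the other way by the same 9-point baseline gap, and the adjusted estimate lies between. The pilot randomised only 151 patients, so a gap that large is not to be expected at 240 per cell.

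A reader might also infer that the model must misfit a one-time exercise. With one follow-up value the mean line is saturated and cannot misfit. With two, a sustained step still returns the full 6-month change, and only decay is missed. The shape point and the random-effects point need different data structures, so they cannot both apply. The random-effects point concerns the covariance, not the mean contrast, and section F allows the covariance structure to be revised.

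Finally, site may be among the covariates not shown, and listing those is commonly left to an analysis plan. Its absence from the displayed model costs about 1 power point or less.

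None of this removes the free baseline difference or settles which of the two named forms is primary.

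**Conclusion.** The point holds as one of efficiency and specification. With one 6-month value, the displayed contrast has 2/(1 + ρ) times the variance of a baseline-adjusted one: 54% more at ρ = 0.3, 33% at 0.5 and 18% at 0.7. In power this is about 17, 10 and 2 percentage points. It falls short of the design's 80% only if ρ is below about 0.5, whereas the adjusted contrast stays above 80% throughout the range examined.

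These figures assume equal variances, 240 evaluable patients per cell, a 0.26 SD effect and complete before-after pairs. The protocol gives no ρ. Chance imbalance of one standard error moves the change estimate by about 0.5 to 1.2 points against a 4.7-point target.

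The loss of a decaying effect applies only if 3- and 6-month values are both modelled on a straight line. The surplus random effects apply only if there is a single follow-up value. The protocol should say which case it intends. The clinic level assumed for the sample size and the provider-only model need to be reconciled, but there is no evidence that the difference matters much numerically.

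**What to change.** Name one primary model in section F, before unblinded outcome data are examined:

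- **One follow-up value:** regress 6-month adherence on arm, race, arm × race, 12-month baseline adherence and site, with a random intercept for provider. As a covariate, baseline need not be a repeat reading of the same quantity, so the 12-month and 6-month windows can differ.
- **If 3-month values are kept, or baseline adherence is missing for some patients:** use a mixed model with categorical time, a common baseline mean across arms within race, and the site-by-race strata.

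Test H1 as the arm contrast in African American patients and H3 as arm × race. Keep the growth curve as an exploratory look at maintenance. State whether clinic is a level of the model, and make *Sample size estimation* and the *Level 3 model* agree.

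The cost is wording plus a rule for missing baseline values. Plain covariate adjustment drops patients without a baseline value, and section F promises to use all available data; the mixed-model form covers that case. Baseline adherence and site are already collected. The site term is there mainly for consistency with the stratified randomisation. It is worth about 1 power point or less in the displayed model, and up to about 2 in the adjusted model under the assumed site trends.

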Following the visit with their provider, patients will complete the post-visit surveys that assess the proposed mediator variables, including 1) a standardized measure of patient activation, 2) a measure of attitude, perceived social norms, perceived behavioral control, 3) a measure of anticipated emotion regarding managing their blood pressure, and 4) a visit satisfaction survey. Patients will receive a \$20 gift card in compensation for participation. Participants must complete the values affirmation exercise in order to receive compensation for participation. Where patients are not able to complete all other surveys at the baseline/index visit, they will have the option of being contacted by study coordinators via phone to complete any remaining surveys, or to complete surveys via a direct web link to REDCap, that can be sent to them via email.

At 3-months, subjects will be called by the research assistant to schedule 3-month visit which includes measures of blood pressure, pill counts, self-reported adherence survey and the proposed mediators of the intervention effect (Table 1). This visit may coincide with a regularly scheduled follow-up visit with their provider. At 6-months, all subjects will return for an in-person visit to have their blood pressure measured by the research assistant and complete a 6-month survey with the same measures as those obtained at 3-months (Table 1). This visit may also coincide with a regularly scheduled follow-up visit with their provider. At the 3- and 6-month visits, patients will also be asked to bring all antihypertensive medications for pill count assessment, and will receive an additional \$20 gift card as compensation for participation. If patients are unable to attend either the 3 or 6-month follow up in person visit, they will be given the option to complete the surveys over the phone, or to complete surveys via a direct web link to REDCap that can be sent to them via email, and their incentive will be mailed to their home.

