### C. Study Design and Research Methods

[figure not shown]

**Overview:** The study design was developed in consultation with providers at the study sites to ensure feasibility of implementation in routine clinical practice. All primary care providers (PCP) at the participating clinics will be invited to complete a baseline survey regarding past disparities training and racial attitudes; patient participation will be independent of whether their PCP

participates. We will enroll self-identified African American and white patients with uncontrolled hypertension who are eligible and consent for the study. Our primary outcome is medication adherence that will be measured in three ways: 1) pharmacy fills, 2) self-report, and 3) pill counts. At the index visit, before they see their PCP, participants will have their blood pressure recorded and will complete a survey which includes a validated self-report measure of adherence (see Table 1 for survey contents). We will also query the EHR for baseline adherence based on prior 12-months pharmacy fills. Participants will be randomized to the values affirmation or control intervention tasks and they will complete the assigned task before seeing their PCP as scheduled. Following the visit, patients will complete a brief survey. Participants will return at 3-months and 6-months for in-person follow-up visits that will include assessment of adherence, blood pressure measurement and completion of surveys. Participants will be asked to bring all antihypertensive medications to each follow-up visit, and fill date and number of pills in the bottle will be recorded. Adherence will be calculated for each antihypertensive drug in the regimen and combined across drugs into a summary measure of adherence for the entire drug regimen. Secondary outcomes include blood pressure, time under blood pressure control, and appropriate treatment intensification. Throughout the study, we will evaluate the intervention for widespread dissemination based on the RE-AIM framework.

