**Table 1: Patient survey contents**

| Pre-visit Survey              | Post-visit survey               | 3- and 6-month surveys        |
|-------------------------------|---------------------------------|-------------------------------|
| Prior discrimination          | Patient Activation Measure      | Patient Activation Measure    |
| Voils adherence questionnaire | Attitudes Survey                | Attitudes Survey              |
|                               | Patient impression of the visit | Voils adherence questionnaire |

**Prior experience of discrimination.** We will treat perceived discrimination as a potential modifier of the effect of the intervention on adherence. We will use a 4-item questionnaire about prior experience of discrimination modified from prior scales measuring lifetime discrimination related to healthcare. Responses are on a 5-point Likert scale ranging from "never" to "all of the time". (see Prior Discrimination Survey-new version)

**Patient activation.** We will also assess the effect of the intervention on patient activation, our theoretical mediator of the effect of values-affirmation on engaging in hypertension care. (Figure 1) We will use a low-literacy version of the 13-item instrument developed by Hibbard, the Patient Activation Measure (PAM). Increases in the PAM are associated with increase self-management behavior including adherence. Patient activation measured with the PAM is lower for African Americans than it is for whites, and is therefore hypothesized to be a contributing factor to racial health disparities. Few interventions have been shown to be effective for increasing patient activation. Each questions is answered on a 4-point Likert scale.

We will treat the PAM score as a potential mediator of the effect of the interventions on adherence and measure this construct after the index visit and at 3- and 6-months to determine maintenance of effect.

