| Provider implicit racial bias                                                                            | Potential Moderator               | Baseline                  | Provider completed survey                                                                |
| Provider past disparities training.                                                                      | Potential Moderator               | Baseline                  | Provider completed survey                                                                |
| Provider self-efficacy regarding care to African American patients.                                      | Potential Moderator               | Baseline                  | Provider completed survey                                                                |
| Provider interracial contact.                                                                            | Potential Moderator               | Baseline                  | Health system administrative data                                                        |
| Patient activation measure (PAM)                                                                         | Hypothesized Mediator             | Baseline, 3- and 6-months | Patient completed survey                                                                 |
| Attitudes survey                                                                                    | Alternative Mediator              | Baseline, 3- and 6-months | Patient completed survey                                                                 |
| HTN medications                                                                                                        | Covariates                        | Ongoing                   | DW - pharmacy records and medication lists                                               |
| Relevant comorbid conditions (diabetes, atherosclerotic cardiovascular disease, heart failure, stroke, kidney disease) | Covariates                        | Ongoing                   | DW, Problem list, claims, clinical diagnoses from visits                                 |

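### The mediation analysis names change in patient activation as its main predictor, but activation is first measured after the exercise and the visit, so that term omits any effect already present by then

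*Protocol*

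**What the plan says.** Section F of the protocol, at the end of the Level 3 model text, sets the mediation analysis for adherence "with *change in adherence* as the primary outcome and *change in PAM scores* (or other measure) as the primary independent variable". The sample size paragraph in the same section is written for the same quantity, claiming over 80% "power to detect a 0.13 partial correlation between change in the patient activation and change in adherence" with 480 patients.

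The timing is given in several places:

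- Section C, Overview: after randomisation, "they will complete the assigned task before seeing their PCP as scheduled".
- Section B, Patient recruitment and procedures, on what is asked before the visit: "Additional surveys will include a baseline demographics questionnaire, a measure of past experiences of discrimination, and a self-reported adherence (Voils) measure". Neither the PAM nor the attitudes survey is listed. The pre-visit column of Table 1 agrees.
- Section B, on what follows: "Following the visit with their provider, patients will complete the post-visit surveys that assess the proposed mediator variables".
- Section C, Patient activation: the investigators will "measure this construct after the index visit and at 3- and 6-months to determine maintenance of effect".
- Table 3 gives the timing of both the PAM and the attitudes survey as "Baseline, 3- and 6-months".

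Adherence is different. Section F defines its time 0 as pharmacy adherence over the 12 months before the index visit, which is a true pre-exercise baseline.

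**The concern.** A change score needs a reference taken before the intervention if it is to carry the intervention's effect. Here the earliest PAM and attitudes scores already follow both the exercise and the visit. Any change that can be formed is a 3- or 6-month score minus a post-exercise score.

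The protocol's mechanism runs through the index visit. Section 1.5 has affirmation improving communication with the provider and thereby activation, and the pilot summary in section 1.7 reports mediation by information exchange during the visit. The Patient activation paragraph treats the later PAM scores as a check on whether the effect lasts, so it expects the effect to be present in the first score. Subtracting that score takes out the part of the effect that the theory predicts.

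At stake is the mediation half of H2. A mechanism that works as hypothesised could appear in the named analysis as absent or reversed. The attitudes-survey mediators have the same timing and the same problem.

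**Working it through.** **1. The plan's own power figures.** Using the Fisher z approximation, power = Φ(atanh(r)·√(n − 3) − 1.96), two-sided α = 0.05:

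- n = 480, r = 0.13: 0.1307 × 21.84 − 1.96 = 0.895, power 81.5%.
- n = 960, r = 0.10: 0.1003 × 30.94 − 1.96 = 1.144, power 87.4%.

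Both agree with the stated figure of over 80%. With 10 adjusting covariates they become 80.7% and 87.0%. The arithmetic is sound; the issue is the variable to which it refers.

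**2. Order of measurement.**

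| Occasion | PAM and attitudes | Pharmacy adherence |
|---|---|---|
| Before the exercise | not collected | prior 12 months |
| Exercise, then visit | – | – |
| After the visit | first score | follow-up begins |
| 3 and 6 months | repeat scores | 6-month follow-up |

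The two change scores in the mediation model therefore span different contrasts. Change in adherence crosses the intervention; change in PAM starts after it.

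**3. What the change score contains.** Let d be the arm difference in PAM at the post-visit survey and k the share of it present at the later visit. Randomisation makes the arms equal in expectation before the exercise.

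- Later minus post-visit (the only change available): kd − d = (k − 1)d.
- Later minus pre-exercise (not available): kd.
- Post-visit level, compared between arms: d.

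The protocol gives no expected effect on the PAM. Taking d = 0.30 SD purely as an illustration:

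| Share retained, k | Later − post-visit | Later − pre-exercise | Post-visit level |
|---|---|---|---|
| 1.50 (grows) | +0.15 | +0.45 | 0.30 |
| 1.00 (sustained) | 0.00 | +0.30 | 0.30 |
| 0.75 | −0.075 | +0.225 | 0.30 |
| 0.50 | −0.15 | +0.15 | 0.30 |
| 0.00 (lost) | −0.30 | 0.00 | 0.30 |

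The sizes scale with d; for any positive d the sign pattern depends only on k.

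**4. Consequence for the indirect effect.** If b is the slope of change in adherence on change in PAM, the indirect effect through the change term is b(k − 1)d. With b positive, this is zero when the activation effect is sustained and negative when it fades.

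**5. What a between-patient term would keep.** If the model also carries each patient's mean PAM over the three occasions, with share m present at 3 months, the arm difference in that mean is d(1 + m + k)/3. For d = 0.30 it is 0.30 when the effect is sustained. With k = 0.50 and m midway at 0.75, it is 0.30 × 2.25/3 = 0.225, with the correct sign.

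**The case against.** The strongest reply is that the change term is not the whole mediation plan. The sentence that names it also calls for methods separating between-patient from within-patient effects, and step 5 shows that a between-patient term can keep much of the signal. The Statistical Analysis text in section F enters activation and the attitude constructs as mediators without calling them change scores. The Patient activation paragraph already plans to examine the intervention's effect on activation. Growth after the visit would also still appear in the change score. All of this stands. A reader might infer that the mediation answer under H2 must come out null or reversed; the documents do not support that. They support the risk for the one term that the protocol designates as primary.

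A second reply is that Table 3 uses baseline to mean the index-visit occasion, much as section B speaks of surveys at the baseline/index visit. That is a fair reading. The label is then loose rather than a separate mistake, but it should not be taken as a pre-exercise value.

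A third reply is that within-patient change removes stable differences between patients, whereas a post-visit level does not. This is a real trade-off and belongs in the fix. It does not restore the effect that the change score leaves out.

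**Conclusion.** The point holds as a mismatch between the named primary mediator term and the measurement schedule. Relative to the immediate effect d, the change term carries (k − 1)d: nothing if the effect is sustained, a negative difference if it fades, and only later growth if it grows. The 0.30 SD and the retention shares are assumptions for illustration. That the first PAM and attitudes scores follow the exercise and visit is stated in the protocol.

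The reach is limited. The primary adherence comparison (H1) and the comparison by race (H3) do not use these scores. The protocol describes its work on mechanisms as exploratory. No data are lost, and the matter can be settled in the analysis. It should be fixed, but it does not threaten the trial's main result.

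A reader might also infer that the mediation power statement is deficient, since an indirect effect needs a path from arm to activation as well. The documents do not support that criticism. The protocol claims power only for a partial correlation, both figures reproduce, and it gives no expected effect on the PAM from which joint power could be computed.

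**What to change.** - Make the post-visit PAM and attitudes level the primary mediator term. Compare it between randomised arms, then relate it to 6-month pharmacy adherence, adjusting for arm, race, baseline adherence and covariates. This score is also placed at the start of the adherence window, whereas change to 6 months runs alongside the outcome.
- Keep change from post-visit to 3 and 6 months as a supporting analysis of whether the effect lasts.
- In Table 3, relabel the timing of the PAM and the attitudes survey as post-visit, 3 and 6 months.

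The cost is analysis wording and two table cells, with no new data. The downside is that, with no pre-exercise PAM, the path from mediator to adherence can be confounded by stable prior activation, and the protocol itself links activation to adherence. State this as a limitation; the supporting change analysis partly offsets it. Section B also lets patients finish outstanding surveys later by phone or web, so report how many post-visit scores were obtained after the index day.
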